## 1. Introduction

### 1.1. Background

Immunoglobulin A (IgA) nephropathy is the most common type of glomerulonephritis. Up to 40% of the patients with IgA nephropathy progress to end stage renal disease (ESRD) within 20 years, making it the leading cause of kidney failure in many parts of the world.

The effective treatment for IgA nephropathy remains uncertain. The central role of the immune and autoimmune activation in the pathogenesis of IgA nephropathy indicates a potential benefit of immunosuppression for treating the disease. However, the efficacy of immunosuppression in IgA nephropathy has been controversial. Current management of IgA nephropathy remains focused on non-immunosuppression-based strategies, i.e. supportive care, to reduce proteinuria and slow the disease progression. This encompasses optimal inhibition of renin-angiotensin system (RAS), rigorous blood pressure control, and lifestyle modification. However, despite intensive supportive care, considerable number of patients still have massive proteinuria and remain at high risk of disease progression. The Kidney Disease Improving Global Outcomes (KDIGO) guidelines suggest the use of systemic glucocorticoids in patients with a proteinuria level of  $\geq 1\text{g/day}$  and an estimated glomerular filtration rate (eGFR) of  $\geq 50\text{ml/min/1.73m}^2$ , despite of 3 to 6 months of optimized supportive care. The benefits of immunosuppressive therapy, particularly when added to supportive care, remain largely unclear.

Mycophenolate mofetil (MMF) is a potent immunosuppressive agent selective for lymphocytes and inhibits antibody production by B cells more than any other immunosuppressants. However, previous reports on the efficacy of MMF treatment in patients with IgA nephropathy are controversial, probably due to the small sample size in most published studies, and differences in patients characteristics, e.g. low or high risk of disease progression, and with or without consistent blockade of RAS.

The present study is designed to test the hypothesis that addition of MMF to the comprehensive supportive care would be superior to the supportive care alone in reducing the risk of clinically important kidney outcomes in patients with IgA nephropathy who are at a high risk of disease progression.

### 1.2. Protocol Version and Amendments

This statistical analysis plan (SAP) is based on the protocol “The Effect of Mycophenolate Mofetil on Renal Outcomes in Advanced Immunoglobulin A Nephropathy” (Clinicaltrials.gov study number: NCT01854814, Protocol version: V2.0, Version date: 15 Nov 2017).

## 2. The Study Objectives

The primary objective of the study is to test if combination of MMF and losartan is more effective than losartan alone in reducing the risk of disease progression in patients with IgA nephropathy.

## 3. Study Design

This study is a prospective, open-label, randomized controlled, blinded endpoint (PROBE) trial. This trial will include participants with IgA nephropathy who are at a high risk of disease progression.

Patients with IgA nephropathy were recruited at the renal division of Nanfang Hospital, Southern Medical University. After recruitment, the patients first entered into a 12-week run-in period, during which the patients were treated with comprehensive supportive care, including blockade of RAS using maximum tolerable daily dose of losartan to reduce blood pressure to a target below 130/80 mmHg and a urine protein excretion (UPE) below 0.75g per day. The participants were also advised for lifestyle modification, including quitting smoking, restricting high-salt intake, and avoiding nephrotoxic drugs. Anemic patients with a hemoglobin level lower than 110g/L were treated with erythropoietin. Statin was used when necessary. Dietary sodium intake were monitored by urinary sodium excretion rate (or chloride excretion rate in patients treated with sodium bicarbonate) measured by 24-hour urine sample.

The patients who were tolerable to losartan (<30% eGFR decline and without hyperkalemia) and proteinuria (0.75-3.5 g/day) at the end of run-in period were randomized to receive MMF plus supportive care or supportive care alone. The MMF plus supportive care group received a daily oral dose of 1.5g MMF for the first 12 months, followed by a maintenance daily dose of 0.75g to 1.0g for at least 6 months. Both MMF plus supportive care and supportive care alone group stayed on supportive care as in the run-in period. All participants were followed up at regular intervals for 3 years.

### 3.1. Study Population

The target population is the patients with IgA nephropathy who are at a high risk of disease progression.

#### **Inclusion criteria for entering run-in period:**

- Adult female or male (18 years of age or older);
- Biopsy-proven primary IgA nephropathy;
- 24 hour urinary proteinuria excretion  $\geq 1\text{g}$ ; and eGFR  $< 60\text{ ml/min/1.73m}^2$ , or persistent hypertension, defined as blood pressure  $\geq 140/90\text{ mmHg}$  in two visits at least one day apart or need of antihypertensive drug;
- Signed informed consent

#### **Exclusion criteria for entering run-in period:**

- Familial IgA nephropathy
- Concomitant disease: cancer, infection, diabetes mellitus, connective tissue disease, abnormal liver function, or liver disease;
- Pregnant women;
- eGFR  $< 30\text{ ml/min/1.73m}^2$ ;
- Prior immunosuppressive therapy;
- Severe hypertension (systolic blood pressure over 180 mmHg and/or diastolic blood pressure over 110 mmHg);
- Serum albumin level  $< 30\text{g/L}$ ;
- Hyperkalemia (blood potassium  $\geq 5.5\text{ mmol/l}$ );
- Inability to comply with study and follow-up procedures.

#### **Inclusion criteria for randomization:**

UPE remained at 0.75-3.5 g per day at the end of run-in period

#### **Exclusion criteria for randomization for randomization:**

Not tolerable to RAS blockade (eGFR decline over 30% of baseline or developing hyperkalemia) during run-in phase

## 3.2. Study Drug

### Drug information

- Drug: Mycophenolate mofetil
- Formulation: Mycophenolate mofetil tablets 0.25g/tablet
- Manufacturer: Hangzhou ZhongmeiHuadong Pharmaceutical Co., Ltd

## 3.3. Treatment Groups

All participants meeting the inclusion and the exclusion criteria were randomized to either MMF plus the supportive care group or the supportive care alone in a 1:1 ratio. Both the participants and the care personnels were aware of treatment assignment. However, the treatment assignments were not disclosed to the members of the endpoint adjudicating committee and the statistical analysis group.

## 3.4. Primary Outcomes

There are two primary outcomes.

1. The time to the first event of the composite outcomes, including:
  - a doubling of serum creatinine, defined as serum creatinine doubled over the baseline and confirmed by another measurement at least four weeks apart; or
  - onset of end stage kidney disease, defined by the need for maintenance dialysis or renal transplantation or kidney failure (defined as  $\text{eGFR} < 15 \text{ ml/min/1.73m}^2$  and need for dialysis or renal transplant, but renal replacement therapy is not available or patients refuse to receive renal replacement therapy); or death due to kidney or cardiovascular cause.
2. The time to progression of CKD, defined by a sustained  $\geq 30\%$  decrease in eGFR and to a level of  $< 60 \text{ ml/min/1.73m}^2$  if the baseline eGFR was  $\geq 60 \text{ ml/min/1.73m}^2$ , or  $\geq 50\%$  decrease in eGFR if the baseline eGFR was  $< 60 \text{ ml/min/1.73m}^2$ . The CKD progression endpoints were also verified by another measurement at least four weeks apart.

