|-----------------------------|---------------------------------------------------------------------------------------------------------------------------------------------------------------------------------------------------------------------------------------------------------------------------------------------------------------------------------------------------------------------------------------------------------------------------------------------------------------------------------------------------------------------------------------------------------------------------------------------------------------------------------------------------------------------------------------------------------------------|
|                             | 
and lower than 3.5g per day, and those who are willing to participate the study entered the 3-year trial phase and will be randomly assigned to MMF plus supportive care or to supportive care alone. Patients who are not tolerable to RAS blockade (eGFR decline over 30% of baseline or developing hyperkalemia) during run-in phase will not undergo randomization.
 
In the trial phase, patients assigned to the MMF group received oral administrated MMF at a daily dose of 1.5g for 12 months and then tapered to a maintained daily dose of 0.75g to 1.0g for at least 6 months. Both MMF plus supportive care and supportive care alone group stayed on supportive care as in run-in period.
 |
| Study size           | 
The sample size is estimated before the study with the use of nQuery Advisor software. Our preliminary study of IgA nephropathy showed that the three-year rate of the primary endpoint (doubling of serum creatinine, end-stage renal disease) among patients with IgA nephropathy taking RAS inhibitors was 36%. It is presumed that MMF treatment will reduce this rate to 16%. Thus, the enrollment of 76 per group will provide the study with a statistical power of 80% at a two-sided significance level of 0.05. Considering 10% of participants lost to follow-up over 3 years, the final sample size was 84 per group.
                                                                            |

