#### 7.4 Sample size

The sample size is estimated before the study with the use of nQuery Advisor software. Our preliminary study of IgA nephropathy showed that the three-year rate of the primary endpoint (doubling of serum creatinine, end-stage renal disease, and death) among patients with IgA nephropathy taking RAS inhibitors was 36%. It is estimated that MMF treatment will reduce this rate to 16%. Thus, the enrollment of 76 per group will provide the study with a statistical power of 80% at a two-sided significance level of 0.05. Considering 10% of participants lost to follow-up over 3 years, the final sample size was 84 per group.

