#### 7.7 Study Outcomes

##### Primary outcomes

1. The time to the first event in the composite outcomes of doubling of serum creatinine, defined as two serum creatinine levels measured at four weeks apart that were twice the baseline value, the onset of end stage kidney disease (ESRD), defined as the need for maintenance dialysis or renal transplantation or renal failure (defined as  $\text{eGFR} < 15 \text{ ml per min per } 1.73\text{m}^2$  and need renal replacement therapy, but renal replacement therapy is not available or the patient refuse to receive renal replacement therapy), and death due to kidney or cardiovascular cause.
2. The time to progression of chronic kidney disease, defined by a decrease in eGFR of 30% or more from baseline and to a level of less than  $60 \text{ ml per minute per } 1.73\text{m}^2$  if the baseline eGFR was  $60 \text{ ml per minute per } 1.73\text{m}^2$  or more, or a decrease in eGFR of 50% or more if the baseline eGFR was less than  $60 \text{ ml per minute per } 1.73\text{m}^2$ . The chronic kidney disease progression endpoints were also verified by another measurement at least four weeks apart.

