**Safety endpoints**

1. Including all adverse events (AEs), serious adverse events (SAEs), study drug-related SAEs, AEs leading to study withdrawal, and AEs related to the study drug occurred during the study period will be recorded.
1. SAEs were defined as death, life-threatening conditions, requiring inpatient hospitalization or prolongation of existing hospitalization.
2. AEs with special concern were defined as drug-related AE listed in the drug information provided by the pharmaceutical manufacture of MMF, including leukopenia or leukocytosis, anemia, sepsis, gastrointestinal symptoms (diarrhea, stomachache, vomiting, anepithymia), certain types of repeated infections (pneumonia, influenza syndrome, urinary tract infection, herpes zoster, etc.), hepatic dysfunction or transaminase elevation, malignancy.

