## **6.3. Efficacy Analyses**

### **6.3.1. Main Analyses of the Primary Outcomes**

- The number of the composite outcome (primary outcome 1) and its components by each treatment group in ITT.
- The number of disease progression (primary outcome 2) by each treatment group in ITT.
- Kaplan-Meier curves of cumulative survival rates of the two primary outcomes by two treatment groups in ITT.
- To perform log-rank tests on the two primary outcomes between the two treatment groups in ITT. A p-value of 0.025 will be regarded as statistically significant.
- Estimate the hazard ratios (and 95% confidence intervals) of the treatment for the two primary outcomes, respectively, using the Cox proportional hazard models, with and without covariate adjustment. The adjusting covariates include age, sex, BMI, SBP, eGFR, logarithm of UPE rate and individual Oxford MEST-C scores at baseline.

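### The plan does not say how deaths from other than kidney or cardiovascular causes are handled, and no planned analysis is assured to compare them between arms

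*Combined protocol and SAP*

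**What the plan says.** **Definition.** SAP 3.4 limits the mortality component of primary outcome 1 to "death due to kidney or cardiovascular cause". Protocol 7.7 agrees ("and death due to kidney or cardiovascular cause"), as do the objectives and outcomes in the protocol abstract. Primary outcome 2 ("The time to progression of CKD, defined by a sustained" fall in eGFR) has no death component.

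**Sample size.** Protocol 7.4 attaches its 36% control rate to "doubling of serum creatinine, end-stage renal disease, and death", with no restriction on cause. The Study size entry of the abstract attaches the same 36% to "doubling of serum creatinine, end-stage renal disease", with no death at all.

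**Analysis.** SAP 6.3.1 plans event counts with the composite's own components, "Kaplan-Meier curves of cumulative survival rates of the two primary outcomes by two treatment groups in ITT", log-rank tests at 0.025, and Cox hazard ratios. SAP 4.3 says that missing endpoint data are not imputed. Neither section gives a censoring rule for other deaths, a competing-risk method or an analysis with all-cause death.

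**Safety.** Protocol 7.7 defines adverse events of special concern as drug-related events from the MMF product information. The list includes sepsis and "certain types of repeated infections (pneumonia, influenza syndrome, urinary tract infection, herpes zoster, etc.), hepatic dysfunction or transaminase elevation, malignancy". SAP 3.7.1 analyses events from first MMF use to 30±7 days after last use. Protocol section 9 (Collection) does not require adverse events to be documented in a patient who has not used MMF. SAP 5.2 leaves patients who took no study medication out of the safety set.

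**The concern.** A patient on MMF who dies of sepsis or cancer before any kidney event adds no event to either primary outcome. Such deaths, if the drug causes them, would fall mainly in one arm. They would hardly move the hazard ratio, and the written safety analysis might not show them as a between-arm comparison either. The trial could then report a kidney benefit with no planned result that sets all deaths beside it. Separately, the documents describe the mortality component of the sizing endpoint in ways that do not match the outcome definition, so it is unclear what the 36% measured.

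**Working it through.** **1. The plan's own figure.** Inputs from protocol 7.4: 36% and 16% at 3 years, two-sided 0.05, power 80%. Pooled two-proportion formula, mean rate 0.26:

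n = [1.96·√(2·0.26·0.74) + 0.842·√(0.36·0.64 + 0.16·0.84)]² / 0.20² = (1.216 + 0.508)² / 0.04 = 74.3, so 75 per group against 76 stated. Then 76 × 1.10 = 83.6, so 84. The stated size reproduces. It contains no separate rate for other deaths.

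**2. What counts as death.**

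| Place | Death component |
|---|---|
| SAP 3.4, protocol 7.7, abstract outcomes | kidney or cardiovascular only |
| Protocol 7.4 | death, cause not restricted |
| Abstract, Study size | none |

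**3. What the planned methods do with another death.** No rule is written, so censoring at death is inferred from ordinary practice. It concerns only patients with no earlier qualifying kidney event. Log-rank and Cox then compare cause-specific hazards, which is valid. One minus Kaplan-Meier, read as a risk, is too high because it treats the dead as still able to reach the outcome. With constant hazards and an assumed 3% of other deaths on MMF:

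- kidney hazard h = −ln(0.84)/3 = 0.0581 per year; other-death hazard k = −ln(0.97)/3 = 0.0102 per year
- cumulative incidence = h/(h+k) × [1 − 0.84·0.97] = 0.851 × 0.185 = 15.8%, against 16.0% from one minus Kaplan-Meier.

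At this rate the overstatement is only 0.2 points.

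**4. Does the safety analysis fill the gap?** MMF is planned for 12 months and then at least 6 more, in 3 years of follow-up. If it stops at 18 months, the safety window closes by about 18 + 37/30.4 = 19.2 months and leaves about 17 of 36 months outside. In the control arm the window has no defined start or end, and section 9 does not require documentation there.

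**5. Effect on power.** The documents give no rate of other deaths, so the rates are assumptions. Simulated log-rank test: 84 per arm, exponential times, 36% against 16% at 3 years, no dropout, 4,000 runs, two-sided 0.025.

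| Other deaths, control / MMF | As written | With all-cause death |
|---|---|---|
| 0% / 0% | 79.1% | 79.1% |
| 1% / 3% | 77.7% | 65.6% |
| 1% / 5% | 77.9% | 56.8% |

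A repeat of the 1% / 3% case with 20,000 runs gave 77.8% and 66.4%. On MMF, 3% and 5% of 84 are 2.5 and 4.2 deaths. The underlying hazard ratio is ln(0.84)/ln(0.64) = 0.39 as written. With all-cause death at 1% / 3% it is (0.0581 + 0.0102)/(0.1488 + 0.0034) = 0.45.

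**6. Effect on a single result.** HR ≈ ln(1−e₁/84)/ln(1−e₀/84) and z = |ln HR|/√(1/e₁ + 1/e₀), with 30 control events and every other death placed on MMF:

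| MMF events | HR | p |
|---|---|---|
| 13 | 0.38 | 0.004 |
| 14 | 0.41 | 0.006 |
| 15 | 0.45 | 0.011 |
| 16 | 0.48 | 0.017 |
| 17 | 0.51 | 0.027 |

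The planned 16% of 84 is 13.4 events. From 14, a third other-cause death passes 0.025; from 13, three give 0.017 and it takes four. In a simulated log-rank test at 17 against 30 events, the median p was 0.0252 and 48% of runs stayed below 0.025.

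**The case against.** The cause restriction is consistent across all the outcome definitions and fits a hypothesis about kidney outcomes. Cause of death goes to a blinded adjudicating committee (protocol 7.6). Entry excludes cancer, active infection, diabetes and liver disease, so few other deaths may occur. All of this stands, and it is why the definition should be kept.

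It can also be said that harm is already visible. Death is a serious adverse event, Table 1 marks adverse events at every visit to week 156, SAP 6.4 compares proportions by Fisher's exact test, and SAP 4.2 lists reasons for premature discontinuation. This stands in part. The visit schedule suggests that deaths may well be known, but section 9 of the protocol does not require documentation without MMF use, SAP 3.7.1 limits what is analysed, and SAP 4.2 does not name death as a reason. Nothing assures a comparison of all deaths between arms.

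A reader might infer more than the documents support:

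- That a patient who dies of sepsis is counted as event-free for 3 years. Under the usual handling the patient leaves the risk set at death.
- That the log-rank and Cox results are therefore invalid. They remain valid comparisons of cause-specific hazards; only their reading as total risk or net benefit is limited.
- That three deaths would overturn the trial. That depends on rounding 13.4 up to 14, on placing every death on MMF and on an approximate test.

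**Conclusion.** The point holds as a gap in the plan, not as a fault in the endpoint. The handling of other deaths is unstated, no efficacy analysis counts them, and the safety analysis does not assure that they are compared by arm. The primary result as written barely responds to such deaths (power within about 1.5 points of 79.1% in the scenarios above), whereas an all-cause version would lose about 12 points at 1% / 3% and about 21 at 1% / 5%. These figures rest on assumed death rates, constant hazards and no dropout; with no such death the effect is nil. The conflict between the two sample-size statements and the outcome definition is a matter of text and needs no assumption. The change is a cheap improvement, and the primary analysis does not depend on it for validity.

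**What to change.** - Keep the definition of primary outcome 1.
- In SAP 6.3.1, state that other deaths are censored at death and that the hazard ratio is cause-specific. Extend the rule to primary outcome 2, where no death counts.
- Pre-specify a supportive ITT analysis of primary outcome 1 with death from any cause as the component, using the same log-rank and Cox methods, and cumulative incidence curves with other death as a competing event.
- Do not turn the supportive analysis into a success criterion. Asking only that it point the same way would not bind: even the most extreme count above has HR 0.51.
- Record vital status in both arms over the full 3 years regardless of MMF use, and list all deaths in the ITT set by arm and adjudicated cause.
- Have the sponsor confirm what the preliminary 36% measured, then reconcile protocol 7.4 and the abstract's Study size entry with protocol 7.7 and SAP 3.4. Until that is known, the wording should not simply be edited to match.

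Cost: confirmation of vital status in both arms, some SAP wording and a little extra output. The supportive hazard ratio will be slightly diluted by unrelated deaths. With 1% added to each arm, two-proportion power at 76 per group and 0.05 falls from 80.9% to 79.9%.

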## 3.6. Secondary Outcomes

There are four secondary outcomes.

- 1) The time to 30% reduction in eGFR from the baseline.
- 2) Annual absolute changes in the eGFR (eGFR slope) over the trial period.
- 3) Rapid eGFR decline ( $< -5 \text{ ml/min/1.73m}^2/\text{year}$ ).
- 4) Percentage change in the rate of urinary protein excretion at the end of trial over the baseline.

## 3.7. Safety Endpoints

### 3.7.1. Adverse Events

#### (1) AEs/SAEs

AEs/SAEs occurred during the study period from the first application of MMF to 30±7 days after the last use of MMF will be analyzed and summarized.

**Adverse event (AE):** Any untoward medical occurrence in a patient with the use of a medical product and which does not necessarily have to have a causal relationship (association) with this product. An AE can therefore be any unfavorable and unintended sign (including an abnormal laboratory finding), symptom, or disease temporally associated with the use of the study device, whether or not related to the product.

**Adverse Reaction (AR):** is defined as a response to the study device which is noxious and unintended. An AR is any AE judged as having a reasonable suspected causal relationship to the study device. The assessment of the causal relationship between an AE and the use of the study device is a clinical decision by the investigator based on all available information at the time of the completion of the CRF. The assessment is based on the question whether there was a "reasonable causal relationship" to the study device in question. Possible answers are "yes" or "no".

**Serious adverse event/serious adverse reaction:** an adverse event (AE) or adverse reaction (AR) is serious if it:

- results in death,
- is life-threatening
- requires inpatient hospitalization or prolongation of existing hospitalization.
- results in persistent or significant disability or incapacity
- is a congenital anomaly, birth defect or fetal mental impairment
- is medically significant: Medical and scientific judgment should be exercised in deciding whether an AE/AR may be considered serious (due to an important medical event) because it jeopardizes the health of the patient or may require intervention to prevent another serious condition (death, a life-threatening condition, hospitalization or persistent or significant disability).

